#### Informed Consent

Participating schools will be asked to send information and active (opt-in) consent forms to parents or guardians of year 9 or year 10 students via hard copy or electronically. Students who receive parental consent will be provided with a web-based participant information statement and consent form and will be required to actively consent before beginning the study. Students who do not consent or who do not receive parental consent to participate in the research trial will still be offered access to the content of the program; however, they will not be prompted to complete assessment surveys, and no data will be collected from those individuals.

### Intervention

#### Overview

The Mind your Mate intervention was collaboratively designed by young people and experts in mental health and substance use prevention. Focus groups were conducted with year 10 students (n=23) from 2 independent secondary schools in Sydney to inform them of the critical components of the development of the mobile app and design. The Matilda Centre’s Youth Advisory Board, a group of young adults who provide feedback on youth-focused projects, guided the initial development and design of the app. Furthermore, each educational module within the app was reviewed by 2 psychologists with expertise on mental health and substance use. The wide range of input from a variety of ages and backgrounds was intended to ensure that the intervention is inclusive and tailored to the needs of adolescents.

Mind your Mate is an mHealth program aimed at upskilling and empowering adolescents to better support their peers about issues on mental health, alcohol, and other drug use. The intervention will include 1 introductory classroom lesson, led by a teacher but delivered on the web, and a downloadable mobile app. It is anticipated that the app will be made available to schools free of charge following the intervention.

#### Classroom Lesson

The Mind your Mate classroom lesson will be web-based through the study website by teachers of the participating schools. Teachers will be provided with an implementation guide containing instructions for accessing the survey, classroom lessons, and an outline of the content links to the NSW Personal Development, Health, and Physical Education Syllabus.

The classroom lesson will take approximately 40 minutes to complete and will be conducted after the students have completed the baseline survey. The lesson introduces common mental health and substance use problems encountered by young people and discusses the concept of supporting peers through animated examples, quizzes, and interactive activities (Figure 2 for example screenshots of these components). The lesson concludes with a video tour of the app’s features and instructions for students to download the app onto their mobile device. Students were instructed to use the mobile app as needed over the following 12-month period.

**Figure 2 figure2:**
[figure not shown]
Screenshot of the Mind your Mate classroom lesson.

#### Mobile App

The Mind your Mate app aims to facilitate discussions among peers and provide key mental health literacy information about anxiety, depression, and substance use (Figure 3). It provides communication tools, educational modules, and suggested activities to engage in conversations and provide support for peers, including the ability to schedule conversations, follow-up, and example messages to send to peers. Several features were included to maintain engagement with the app based on feedback from the focus groups. These included emphasis on visual content such as infographics and videos rather than text, user experience customization through avatar selection and color scheme, gamification of content, and interactive features such as mood tracking and customized self-care activities. Automated pop-up reminder notifications were programmed to maintain their engagement. The reminders appear on the user’s phone home screen and are related to scheduled conversations with friends and the completion of the education modules. Digital metrics will be collected to measure engagement with the app, including uptake, frequency of usage, time spent in the app, and the features and modules that were accessed.

An overview of the Mind your Mate app content is provided in Table 1. The app is self-paced and only accessible to the participants in the intervention group in this study. Within the app, it is emphasized that students are not responsible for their friends or their friends’ choices. Students are encouraged to contact a responsible adult or health professional if they are concerned about their friends. Crisis helpline numbers are easily accessible on the home screen and under support options.

**Figure 3 figure3:**
[figure not shown]
Screenshot of the Mind your Mate mobile app.

**Table 1 table1:** Overview of the educational module content of the Mind your Mate smartphone app.

Module name	Key content covered	Related features
Mental health	Anxiety and depression literacy	Animated videos featuring personal stories Symptom diagrams Myth buster
Stressful times	Management of well-being References to COVID-19 pandemic and bushfires	Links to trusted external resources for self-help and emergencies
Alcohol and drugs	Substance use literacy, normative use, and standard drinks	Animated videos Symptom diagram Quiz question External link to standard drinks calculator
Listen up	Active listening skills Tips and tools to start conversations with friends	Scheduling conversations that link directly into calendar Example text to send to friends
Keeping friends safe	Harm minimization for substance use and supporting disclosure to parents or professionals	Recovery position diagram Video challenging fears of responsibility for a mate Harm minimization and emergency response video
Tricky conversations	Active questioning, motivational interviewing, and communication skills	Conversation preparation checklist and template Template messages to send to friends when reaching out Emotion dictionary
Checking in	Following up with friends and conversation tips	Scheduling follow-up conversations with friends directly into calendar Support links Profiles for friends to reference upcoming and past conversations
What next?	Challenges notion of having sole responsibility for another’s well-being and supporting disclosure to parents or professionals	Template to review conversation with friend Interactive checklist Textbox for reflection
Support options	Provision of formal and informal support options such as school counsellor, parent, free web-based resources, and general practitioners	Template messages to send to friends when reaching out Links to trusted external educational sites, resources, and support
Looking after yourself	Self-care Emotion regulation skills	Personalization of self-care activities list Ability to add custom activity Mood tracker

#### Active Control Group

Control schools will be asked to continue to implement their usual health and physical education classes for the 12-month trial period. The year 9 and year 10 Health and Physical Education curriculum mandates that content on alcohol and other drug use and well-being be implemented. As such, all control schools will implement curriculum-based health education during the trial. This group will serve as the *active control*. Although no app component will be offered to control schools during the trial, complimentary use of the intervention at the end of the study, if effective, will be available.

#### Assessment Occasions

All students (intervention and control conditions) will be asked to complete a web-based self-report survey in a supervised classroom setting at baseline and 6 and 12 months after baseline. Students completing web-based surveys will be assigned a unique participant identifier generated in REDCap (Research Electronic Data Capture; Vanderbilt University), a secure web-based data collection system. This identifier will be used to email students with personalized survey links that they will use to complete each survey. This unique code links student data over time while maintaining confidentiality. Absent students will be contacted by the research team (using details provided upon registration) and invited to complete the survey at a later date. Students will be made aware that all the contact information they provide will be kept strictly confidential and secure, separate from their survey responses. After each survey, students will be incentivized with entry into a draw for 1 of 5 Aus $50 (US $38) Prezzee gift vouchers (5 vouchers per assessment occasion).

### Measures

#### Overview

Demographic data, including age, sex, gender, home postcode, and country of birth, will be obtained to determine the baseline equivalence of the groups. To assess academic performance, students will nominate the range that their grades usually fall into (ie, <49%, 50%-59%, 60%-69%, 70%-79%, 80%-89%, and 90%-100%). Truancy will be measured by students reporting the number of days that they had off from school in the previous year without their parents’ permission.

#### Primary Measures

##### Knowledge

Mental health and substance use knowledge specific to content within the mobile app will be assessed using a questionnaire developed by the research team (Multimedia Appendix 1). General mental health literacy will be assessed using questions adapted from the Mental Health Literacy Questionnaire [42].

##### Alcohol and Other Substance Use

Drinking behavior in the past 6 months will be assessed by using questions adapted from the School Health and Alcohol Harm Reduction Project Patterns of Alcohol index [43] and reflect those used in previous trials the team has led [44]. Students will be asked to report the frequency and quantity of alcohol consumption in standard drinks, proportion of friends who drink, and intentions to try alcohol. A pictorial standard drink chart will be supplied within the survey to assist students in identifying what constitutes a standard drink in common portions and the types of alcohol [45].

The reasons for not drinking alcohol will be assessed using the Motives for Abstaining from Alcohol Questionnaire [46]. Students will be asked to rate how important each statement is to them personally, with response options ranging from *not at all important* to *extremely important*.

Other substance use will be assessed using questions adapted from the Australian Institute of Health and Welfare: National Drug Strategy Household Survey [47]. Students will be asked to indicate whether they have ever tried tobacco, vaping, cannabis, ecstasy, cocaine, or methamphetamines; the nonmedical use of prescription drugs; or a combination of drugs at the same time. Students will further be asked how likely it is that they will try any of the listed drugs in the future and the proportion of friends and acquaintances who use drugs.

##### Mental Health Measures

Psychological distress in the past month will be assessed using the Kessler 6 scale [48]. Depression and anxiety symptoms during the past 2 weeks will be measured using the Patient Health Questionnaire 8 [49] and the Generalized Anxiety Disorder 7-item scale [50], respectively.

##### Help-Seeking Measures

The General Help-Seeking Questionnaire [51] will be used to assess future help-seeking behavioral intentions from various sources. A list of potential sources of help will be shown. Students will first be asked to indicate how likely it is that they would seek help from each of these sources for personal or emotional problems, then how likely it is that they would seek help from each of these sources if they were experiencing suicidal thoughts. Responses will be given using a 7-point scale ranging from *extremely unlikely* to *extremely likely*.

Recent help-seeking behavior in the past 2 weeks will be measured using the Actual Help-Seeking Questionnaire [52] and questions adapted from the Mission Australia Report, 2018 [53]. Students will be asked to indicate whether they have sought help from a list of sources in the past 2 weeks. If they select *yes*, they will be asked to briefly describe the type of problem that they sought help for.

#### Secondary Measures

##### Positive Well-being

The impact of the intervention on positive well-being will be assessed using measures adapted from the Warwick-Edinburgh mental well-being scale [54]. Students will be asked to read three statements, such as “I have been feeling good about myself,” and tick the response that best reflects their experience of that statement in the past 2 weeks. Response options range from *none of the time* to *all of the time*.

##### Quality of Life

The Pediatric Quality of Life questionnaire [55] will be used to measure participants’ self-reported quality of life. Students will be asked to complete the questions from the perspective of their own health that day, such as “I don’t feel worried today.”

##### Impact of COVID-19 Pandemic

The impact of the COVID-19 pandemic on physical and mental health will be assessed using measures adapted from the Australian National COVID-19 Mental Health, Behaviour and Risk Communication Survey [56].

### Fidelity and Implementation Log

Students in the intervention group will be asked to provide feedback on their experience and the use of the mobile app, as well as suggestions they may have for improvement, at the 6- and 12-month follow-up occasions. In addition, one teacher at each participating school will be asked at the 12-month follow-up to complete a logbook documenting any additional mental health or alcohol and drug education that was implemented over the course of the study. The logbook will be used to control for the effects of additional well-being programs. Digital metrics of mobile app engagement will also be collected.

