#### Randomization

Following the school principal’s approval, randomization and stratification according to gender will be conducted by a biostatistician external to the research team using the blockrand function in R (R Core Team). The school gender mix for stratification will be coeducational, predominately male, or predominately female, and the threshold for predominately male or predominately female will be at >60%. Half of the schools (n=7) will be randomly allocated to the Mind your Mate intervention condition and half (n=7) to an active control group (health education as usual). Similar to school-based interventions of this kind, students and teachers will not be blinded to intervention allocation.

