### Statistical Analysis

Analyses will use an intention-to-treat approach, including all available measurements for all students, in the groups in which they were randomized. Baseline equivalence and attrition between groups will be examined using single-level analyses, one-way analyses of variance to examine normally distributed data, chi-square analyses to examine binominal data, and Mann-Whitney *U* tests to examine nonnormally distributed data. The baseline data of the primary outcomes will be used as covariates to ensure that any differences between groups at baseline are accounted for. To examine intervention by time interaction–effects, mixed-effects regression will be used because of the multi-level nature of the data (students nested within schools). Hypothesized intervention effects will primarily be examined using mixed-effects linear regression analyses for normally distributed data and mixed-effects logistic regression analyses for categorical data. Bonferroni adjustments will be made for multiple comparisons where appropriate. Multiple imputation and regression weighting strategies will be used to examine the impact of attrition. Sensitivity analyses will be used to assess the effect of attrition on inferences drawn from the target parameters in the statistical analyses**.**

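### The plan to control for extra well-being programmes from a 12-month teacher logbook is unrestricted; this post-randomisation variable should be kept out of the primary models

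*Protocol article*

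**What the plan says.** Under Fidelity and Implementation Log, "one teacher at each participating school will be asked at the 12-month follow-up to complete a logbook". The logbook documents "any additional mental health or alcohol and drug education that was implemented over the course of the study". Its purpose is then given: "The logbook will be used to control for the effects of additional well-being programs". The section does not say which outcome, model or tier of analysis this applies to.

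Four other parts of the article bear on it:

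- **Randomization:** "students and teachers will not be blinded to intervention allocation".
- **Active Control Group:** "Control schools will be asked to continue to implement their usual health and physical education classes for the 12-month trial period". The article states no limit on extra programmes in either arm.
- **Statistical Analysis, principle:** "Analyses will use an intention-to-treat approach, including all available measurements for all students, in the groups in which they were randomized".
- **Statistical Analysis, covariates:** the only covariates named are baseline values of the primary outcomes. The logbook is not mentioned, either as a covariate or as part of a sensitivity analysis.

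**The concern.** Adjusting for a variable measured before randomisation leaves the meaning of the treatment coefficient intact. Adjusting for one that arises after randomisation may not. What the logbook records is taught during the trial, in schools that know their allocation, and is reported by a teacher who also knows it. A control school might bring in something extra because it is waiting for the app. An intervention school might drop content it now thinks redundant, or add more because interest has risen.

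If anything of this kind happens, uptake of extra programmes is partly a consequence of allocation, and two things follow from conditioning on it. The part of the allocation effect that runs through those programmes is taken out of the estimate. A path also opens through unmeasured school characteristics, such as general engagement with student well-being, that influence both programme uptake and student outcomes. The adjusted coefficient is then neither the total effect of allocating a school to the intervention nor a well-defined direct effect. School engagement is not among the measures listed, so the size of the problem could not be judged from the trial's own data.

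**Working it through.** **There is no plan figure to reproduce.** The point concerns the structure of the adjustment. The only inputs from the article are the target difference of 0.2 SD and the planned 14 schools, 7 per arm, with about 60 students each. All uptake rates and programme effects below are assumptions.

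**Formula.** Let p_C and p_I be the proportions of control and intervention schools with an extra programme, and c the coefficient of that programme in the adjusted model. For a linear model with arm and programme as terms,

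adjusted − unadjusted = c × (p_C − p_I).

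If nothing unmeasured drives both uptake and outcome, c is the programme's own effect g. Otherwise c also carries that confounding. When uptake is equal in expectation the difference is zero, whatever c is.

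**Large-sample illustration.** School-level outcomes were simulated for 200,000 schools with a direct intervention effect of 0.2 SD, a programme effect g, and an unmeasured school factor with SD √0.02 on the outcome scale. Uptake either did or did not depend on that factor. Positive values mean benefit.

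| Uptake, control / intervention | g (SD) | Uptake depends on school factor | Total effect | Adjusted | Difference |
|---|---|---|---|---|---|
| 40% / 40% | 0.2 | yes | 0.20 | 0.20 | 0.00 |
| 50% / 30% | 0.1 | no | 0.18 | 0.20 | +0.02 |
| 50% / 30% | 0.2 | yes | 0.16 | 0.23 | +0.07 |
| 60% / 20% | 0.1 | no | 0.16 | 0.20 | +0.04 |
| 60% / 20% | 0 | yes | 0.20 | 0.27 | +0.07 |
| 60% / 20% | 0.2 | yes | 0.12 | 0.27 | +0.15 |
| 30% / 60% | 0.2 | yes | 0.26 | 0.15 | −0.11 |

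The sixth row agrees with the formula: c was 0.366, and 0.366 × (0.6 − 0.2) = 0.146. Reversing the two uptake rates reverses the sign, so about 0.15 SD is possible in either direction under these assumptions. The fifth row shows that a shift arises even when the extra programme does nothing, purely through the unmeasured factor. Without the adjustment, the contrast equals the total effect in every row.

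**What a single small trial can show.** Suppose 4 of 7 control and 2 of 7 intervention schools add a programme worth 0.2 SD. Adjustment moves the estimate by 0.2 × (4/7 − 2/7) = 0.057 SD, which is 29% of the target. That is not evidence of bias. With 6 adopting schools among 14 and no effect of allocation, the probability of an exactly even 3–3 split is C(7,3) × C(7,3) / C(14,6) = 1225/3003 = 0.41. A split at least as uneven as 4–2 therefore occurs by chance 59% of the time.

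**Precision in the same example.** Assume an intracluster correlation of 0.02 (the article gives none) that includes the programme's contribution.

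- Variance of a school mean: 0.02 + 0.98/60 = 0.0363.
- Mean within-arm variance of uptake: (12/49 + 10/49)/2 = 0.2245. The programme explains 0.2² × 0.2245 = 0.0090.
- Correlation of arm with uptake: 14/√2352 = 0.289. Inflation factor: 1/(1 − 0.289²) = 1.09.
- After adjustment: (0.0363 − 0.0090) × 1.09 = 0.0298, about 18% lower than 0.0363.

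Losing one of 12 between-school degrees of freedom moves the critical t only from 2.18 to 2.20. In this example the adjustment gains precision.

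**The case against.** The strongest reply is that nothing puts the logbook in the primary model. The sentence stands in a section on fidelity, the Statistical Analysis section lists other covariates, and a full protocol or analysis plan that is not shown may confine the adjustment to a secondary role. This stands as a limit: a reader might infer that the primary estimate will be logbook-adjusted, and the article does not say so. It does not remove the point, because the sentence as published is an unqualified commitment that the analysis section neither repeats nor restricts.

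Second, bias needs allocation to alter uptake or reporting, and the article reports no such effect. That also stands. Differential uptake is an inference from unblinded schools and measurement after allocation.

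Three stronger readings are tempting and not supported:

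- **That the adjustment removes the comparator itself.** The logbook covers education that is additional, whereas the comparator is the usual health and physical education classes.
- **That it breaches intention to treat as the article words it.** That wording concerns which students and measurements are included and in which groups. Adding a covariate changes neither. The narrower complaint is that the coefficient may no longer be the total effect.
- **That it must cost precision.** Under the assumptions worked above, it gains some.

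**Conclusion.** The point holds in a limited form. The article commits, without restriction, to adjusting for a school-level variable that arises after allocation and is reported by unblinded staff. If uptake or reporting of extra programmes differs by arm because of allocation, the adjusted estimate can depart from the total effect of allocation. Over the assumed range the departure is 0 to roughly 0.15 SD in either direction, against a target of 0.2 SD. It is zero if uptake and reporting are unaffected by allocation. The upper end needs both a 40-percentage-point difference in uptake and an unmeasured common cause, so it marks the edge of the assumed scenarios and is not a forecast.

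The documents do not show that the primary analysis is biased. They show two sections that need to be reconciled, and a specific, cheap change that removes the risk.

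**What to change.** Replace the sentence on the logbook's use, and bring the Statistical Analysis section into line, so that together they say:

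- the logbook variable does not enter the primary models;
- logbook content is reported by arm, as a description of what each arm received beyond its allocated condition;
- any model adjusted for logbook content is labelled exploratory or sensitivity, with a note that the covariate is measured after randomisation.

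Logbook collection is unchanged. The cost is a few sentences, plus whatever precision the adjustment would have brought to the primary model (about 18% of the school-mean variance in the assumed example, and possibly nothing). The article reports that baseline assessments were still under way at submission, so at that stage the change could be made before any 12-month outcome or logbook data existed.
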